***Immunogenicity***

Both ITT and ATP cohorts will be analysed, using immediate *ex vivo* and cultured ELISpots, and ICS data. Geometric means and medians of T cell numbers with 95% confidence intervals for central tendency will describe groups.

***Demographic data.***

Age, location of residence, PCR at day 0 and bed net use will be presented by treatment group to ensure comparability.

***Efficacy***

Efficacy will be analysed both ITT and ATP. Cox regression model analysis of incidence of PCR positivity will allow assessment of the time to first episode as the primary outcome. Various thresholds for PCR positivity will be included for comparison. Age, bed net use and location of residence will be used as covariates. Immunological responses will also be examined as covariates to look for correlates of immunity. These analyses will also be undertaken as a metaanalysis of the combined results of VAC046 and VAC047.

The full analysis plan will be approved by the DSMB before implementation.

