After consent is obtained, each consented volunteer will be screened for clinically significant acute or chronic disease, using both general physical examination and screening laboratory tests (full blood count (FBC), Hepatitis B, alanine transaminase (ALT) and creatinine. The findings at screening will be used to determine whether or not the volunteer is eligible to participate in the trial. Volunteers eligible to participate in the trial will meet all of the inclusion criteria and none of the exclusion criteria (listed below). Likelihood of migration will be an important factor in determining eligibility to participate in the trial. All volunteers will be informed of results of laboratory tests and referral to an appropriate health facility done where necessary. Volunteers will be informed of the need to conduct anonymous HIV testing. All volunteers will receive pre-test counselling from a trained counsellor who will also do post-test counselling after giving the results. HIV positivity will be an exclusion criterion. In order to maintain the confidentiality of those volunteers infected with HIV, we will make it clear that during screening one can be excluded due to a range of diseases (not just HIV) as well as abnormal laboratory results. Enrolment (receipt of first vaccination) will be done within 90 days of screening. Volunteers enrolled will be given photo identity (ID) cards for ease of identification and also to serve as a reminder of the appointment dates. These will be destroyed at the end of the study.

Vaccination, observation and blood sampling will occur at King Baudouin hospital.

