### **Blood sampling**

More detailed immunological studies (details below) will be conducted on a nested cohort, which will require larger volume blood draws at certain time points (details below). In order to identify this nested cohort, participants will be further divided into 2 sampling groups: Group A (30 participants) and B (90 participants). Allocation to sampling groups (i.e. A vs. B) shall be done randomly and stratified by vaccination group (i.e. 1 ChAd63/MVA ME-TRAP vaccinee for each control vaccinee). See tables 2 and 3 below.

20 mls of blood will be collected at screening (similar for both sampling groups) to test eligibility, which will be used for;

- Full blood count
- Serum ALT and creatinine
- HIV antibody testing (pre vaccination only) and Hepatitis B surface antigen
- Baseline *P. falciparum* PCR assay

40 mls of blood will be collected on days 0, 14, 63 and 161 for group A and at day 63 for group B. The following tests will be performed at these time points;

- Full blood count
- Serum ALT and creatinine

- Cellular immunology studies
- Plasma for antibody studies of immunity to malaria antigens.

10 mls of blood will be collected at day 56 for group A and at days 0, 14, 56, and 161 for group B. The following tests will be performed at these time points;

- Full blood count
- Serum ALT and creatinine

10mls of blood will be collected at Days 1 and 57 for Group A and stored for possible future gene expression studies.

Blood samples will be collected at day 63 and then between day 70 and day 119 for PCR monitoring. From day 70, blood samples will be collected three times per week for 4 weeks and then once per week for a further 4 weeks. Each blood sample will be taken by fingerprick (volume, 0.5-1.0ml), or, if the volunteer prefers, by venepuncture (volume, 2ml). See table 4 below for details of timing.

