### **D0 (Vaccination with ChAd63 ME–TRAP or Rabies vaccine) (Clinic visit)**

Medical history, temperature monitoring +/- physical examination will be performed and eligibility reviewed by the study clinicians prior to vaccination. Venepuncture for exploratory immunology (for 30 volunteers), safety assessment (FBC, ALT and Creatinine- all participants) and baseline PCR for *P. falciparum* for all participants will also be done prior to vaccination.

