## **13. STATISTICS**

### **Sample Size Considerations**

The efficacious malaria vaccine RTS,S/AS02 has been subjected to sporozoite challenge studies in non-immune volunteers (62) as well as field trials in adults in the Gambia (30). In sporozoite challenge, RTS,S/AS02 appears to give 32% sterile protection and 30% partial protection. Efficacy was higher in semi-immune adults in field studies, with 70% during the first 9 weeks of follow up.

Vaccine efficacy of ChAd63/MVA ME-TRAP in sporozoite challenge studies in Oxford was 21% sterile protection with 36% partial protection. We therefore consider it plausible that ChAd63/MVA ME-TRAP might show 50% efficacy in field studies of adults.

Assuming 50% efficacy of vaccination, with an estimated 70% local incidence of malaria by PCR during the follow up period, we expect 93% power to detect, at  $p=0.05$ , an efficacy of 50% and 77% power to detect an efficacy of 40% with 100 volunteers. Allowing for up to 20 volunteers to be lost to follow up, our sample size would be 120.

Below we tabulate the power obtained with differing vaccine efficacies and rates of PCR positivity, assuming  $p=0.05$  and 100 evaluable volunteers completing the study.

It should be noted that the incidence of asymptomatic parasite carriage detected by qPCR was taken to be 70% on the basis of two observations in the literature.

- a) The qPCR technique was used in the Gambia to assess the impact of prospective vaccines on 102 volunteers. The results of follow-up over five months showed that 71% of the volunteers became positive again at some time or other during follow-up (Imoukhuede et al. 2007; see paper attached). We also include a second article by Andrews et al. highlighting the excellent sensitivity of this real-time PCR method.

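### The primary Cox model leaves out day-0 P. falciparum PCR, a baseline variable already planned for every volunteer; adding it costs almost nothing and may give a modest gain, and its sampling day needs reconciling

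*Protocol*

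**What the plan says.** **The model.** Section 13 (Efficacy) makes Cox regression of time to first PCR-defined infection the primary analysis and names its covariates: "Age, bed net use and location of residence will be used as covariates". The same section says that a full analysis plan will be approved by the DSMB.

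**The comparability table.** Section 13 (Demographic data) lists the same three variables plus one more: "Age, location of residence, PCR at day 0 and bed net use will be presented by treatment group to ensure comparability".

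**Where the baseline PCR is drawn.** The protocol gives two answers.
- *Day 0.* The D0 visit description says that the baseline PCR "for all participants will also be done prior to vaccination". Table 4 (Summary of study visits) marks PCR at D0 and not at screening. The screening visit description lists no PCR.
- *Screening.* The Blood sampling section says "20 mls of blood will be collected at screening (similar for both sampling groups) to test eligibility, which will be used for" and includes "Baseline *P. falciparum* PCR assay" among those uses. Its day-0 test lists, for both sampling groups, contain no PCR.

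The two days can be far apart: "Enrolment (receipt of first vaccination) will be done within 90 days of screening".

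**The concern.** The plan treats day-0 PCR as important enough to tabulate by arm, then drops it, and only it, from the model. Of the four variables it is the only direct measurement of infection. If carriers at day 0 differ in their later risk of infection, whether because they are more exposed or more immune, three things follow:

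- A Cox model without the variable estimates a hazard ratio pulled towards 1.
- The comparison loses some precision.
- A chance difference in carriage between arms shifts the estimate. Randomisation takes account of area of residence but not of PCR status, so nothing in the design balances carriage. The table would show an imbalance with no prespecified way to handle it, which invites adjustment after the fact.

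The sampling-day discrepancy bears on the same variable. A site that followed only the Blood sampling section could hold a result up to 90 days older than the one that the comparability table names.

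**Working it through.** **Step 1. Reproduce the stated power.** Inputs from Sample Size Considerations: 70% incidence in controls, 50% efficacy, "assuming $p=0.05$ and 100 evaluable volunteers completing the study". With 1:1 allocation that is 50 per arm. Sidedness is not stated; two-sided is used here.
- Risk in vaccinees: 0.70 × (1 − 0.50) = 0.35.
- Two-sided Fisher exact power, 70% against 35%: 93.1% (stated: 93%). At 40% efficacy it is 77.0% (stated: 77%), and at 30% it is 50.5% (stated: 50%). All 12 cells of Table 8 agree within 1 point.

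So Table 8 is an unadjusted comparison of two proportions, with efficacy defined as a ratio of risks. The choice of Cox covariates does not affect it.

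**Step 2. Put the design effect on the Cox scale.** With proportional hazards, the hazard ratio implied by the risks is

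ln(1 − 0.35) / ln(1 − 0.70) = 0.431 / 1.204 = 0.358.

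Expected events: 50 × (0.70 + 0.35) = 52.5. Schoenfeld: z = √(52.5/4) × |ln 0.358| = 3.72, so power = Φ(3.72 − 1.96) = 96.1%.

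**Step 3. Add baseline PCR.** Simulated Cox models: 50 per arm, exponential infection times, control incidence held at 70%, 3,000 runs per scenario, fitted with and without a binary baseline PCR term.
- *Prevalence at day 0:* the protocol has no PCR figure for the site. Its Kenyan extrapolation suggests about 60%; 30% was also run.
- *Hazard ratio for later infection, carriers against non-carriers:* assumed at 1, 1.5, 2 or 3, because the protocol gives none.

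Power without → with baseline PCR, prevalence 60%:

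| Prognostic HR | Efficacy 50% | Efficacy 40% | Efficacy 30% |
|---|---|---|---|
| 1 | 95.8 → 95.7% | 83.9 → 83.5% | 59.9 → 59.7% |
| 1.5 | 95.2 → 95.5% | 84.4 → 85.4% | 60.3 → 62.4% |
| 2 | 96.1 → 96.8% | 83.5 → 86.1% | 61.1 → 64.3% |
| 3 | 96.2 → 98.2% | 84.4 → 90.3% | 61.0 → 70.5% |

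At prevalence 30% and prognostic HR 3: 95.8 → 98.6%, 84.6 → 91.2% and 62.1 → 71.3%. Monte Carlo error is about 0.4 to 0.9 points.

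Attenuation at prevalence 60%, prognostic HR 3, efficacy 50%: mean vaccine HR 0.35 unadjusted and 0.32 adjusted.

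**Step 4. Chance imbalance.** With 60 per arm, allocation unrelated to carriage and prevalence between 30% and 60%, an exact binomial calculation gives a 27% to 32% chance that the arms differ by 10 points or more in day-0 positivity. To a first approximation, a 10-point difference multiplies the unadjusted vaccine HR by exp(0.10 × ln 2) = 1.07 if the prognostic HR is 2, or exp(0.10 × ln 3) = 1.12 if it is 3. The direction depends on which arm has more carriers.

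**Step 5. Sampling day.** The D0 visit description, Table 4 (Summary of study visits) and the comparability table all say day 0. Only the Blood sampling list says screening.

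**The case against.** **No evidence that the variable is prognostic.** The protocol reports no association between day-0 PCR and later infection. Parasitaemia is cleared on days 63 to 65, surveillance starts ten weeks after day 0, and the effect of natural immunity on re-infection is itself a secondary objective. This stands: the gain is conditional, and even the direction of the association is open. The direction need not be known, however. A separate simulation with true HR 0.5 gave similar gains when carriers were assumed to be protected.

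**Wrong comparator.** The calculations compare no adjustment with adjustment for PCR alone. The planned model already has age, bed net use and residence, which may carry part of the same information. This also stands: the increment over the planned model was not estimated and may be smaller.

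**Larger figures can be produced.** A reader who takes 50% efficacy as a hazard ratio of 0.5 might infer a substantial loss. With prevalence 50%, that gives power of 69% rising to 74% at a prognostic HR of 2, and 65% rising to 75% at 3. The documents do not support that as the design case, since Table 8 reproduces as 70% against 35%, a hazard ratio near 0.36.

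**The analysis plan can settle it.** Covariates are often finalised there. But this protocol names its covariates, so the point concerns a stated choice.

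**The day-0 lists prove little.** The Blood sampling section's day-63 list also omits PCR, although the same section schedules PCR on day 63. The lists are not exhaustive, so the missing day-0 entry is weak evidence. The discrepancy rests on the baseline PCR being placed under screening.

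**Conclusion.** The point holds as a nearly free improvement to a stated model and a minor reconciliation of text. The randomised comparison remains valid without day-0 PCR, and the 93% is unaffected.

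For an assumed prognostic hazard ratio of 1 to 3, and measured against an unadjusted model, adding day-0 PCR gains about 0 to 3 points of power at 50% efficacy and up to about 10 points at 30% efficacy. The 10-point figure needs a prognostic hazard ratio of 3. If PCR is not prognostic, the gain is nil and the cost in the simulations is within noise. The simulations assume exact event times and no dropout.

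A reader might infer that power is certainly being lost, or that PCR predicts infection better than age or bed net use. The protocol supports neither statement. What it does support is that the value is planned for everyone before vaccination, is judged worth tabulating, and has no prespecified role if the arms differ on it.

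**What to change.** 1. In section 13 (Efficacy), add day-0 P. falciparum PCR result (positive/negative) to the prespecified covariates of the primary Cox model, and carry it into the analysis plan before unblinding.
2. State that the day-63 PCR is not used for this adjustment, because it is taken after both vaccinations and could be affected by them.
3. In the Blood sampling section, reconcile the line that places the baseline PCR in the screening draw with the D0 visit description, Table 4 (Summary of study visits) and the Demographic data paragraph, which place it at day 0 for all volunteers.

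The cost is one model term and one corrected entry in the sampling list. The D0 visit and Table 4 already provide for the sample, so no new data are needed.

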## **14. TIME FRAME**

### **Pilot Study**

Not applicable

### **Definitive study**

Community sensitization, setting up of laboratory, test ELISPOTS, ICS and PCR assays, consent and screening procedures April 2012 to July 2012

Vaccination and follow-up Commencing July 2012

Data analysis 1st to 2nd Quarter 2013

## **15. ETHICAL CONSIDERATIONS**

### **Human subjects**

#### **Good Clinical Practice**

This trial will be conducted in accordance with the Declaration of Helsinki as agreed by the World Medical Association General Assembly (Seoul 2008), ICH Good Clinical Practice and local regulatory requirements.

#### **Ethical Review**

Before the inclusion of the first subject in the study, the protocol and the informed consent must be approved by the Ethical Review Committee in Senegal and the Oxford Tropical Research Ethics Committee (OXTREC).

The volunteer should give written informed consent before being included in the trial, after having been informed of the nature of the trial, the potential risks and their obligations. Informed consent forms will be provided in duplicate (original kept by the investigator, one copy kept by the subject or the subject's legally acceptable representative).

#### **Confidentiality**

Personal information of the volunteers will be handled confidentially. The principal Investigator will ensure confidentiality of personal data in accordance with ICH GCP and the Declaration of Helsinki (including staff handling the data). Blood samples will be coded with the volunteers study identification number and no personal details will be included so that information can not

be linked to the volunteers. Blood test results will be linked to personal identifying information only on documents held securely in the Clinical Trials Facility. No personal information will be entered into the electronic database, which will identify subjects by their unique code number only. All HIV tests and HIV related referrals will be handled with particular sensitivity. They will not be recorded in the CRF, but will be held securely in a separate document held by the Principal Investigator.

Any future research related to the data or samples from this study will require written scientific and ERC approval before it can be done.

### **Feedback of information**

After the study we expect to hold a series of meetings with initial groups involved with sensitization, to relay feedback on the key findings of this study.

### **What risks may be involved?**

The general risks to participants are those associated with blood sampling and vaccination. Mild local tenderness and bruising, light-headedness, or rarely vasovagal syncope, may result from venepuncture. As with any invasive procedure, infection is also a risk. This risk is minimized by the use of pre-packaged sterile equipment and careful attention to proper technique. There is no risk of HIV infection from phlebotomy since all needles are disposed of after a single use. While performing the procedure, loss of vacuum or collapsed vein might necessitate another draw.

Potential risks from vaccination include local and systemic reactions, which shall be solicited for in this study. Local symptoms including discomfort/pain, redness, swelling, and tenderness at the site of injection may be experienced by the volunteers. Systemic symptoms including myalgia, arthralgia, fatigue, malaise, headache, nausea, vomiting, fever or feverishness may be experienced by the volunteers.

### **ChAd63 ME-TRAP**

To date, 186 volunteers have received ChAd63 ME-TRAP. Local adverse events such as pain would be expected to occur frequently. Less frequent local adverse events are likely to include erythema, swelling and warmth. Local adverse events are likely to be mild in nature and should resolve rapidly. Common systemic adverse events post viral vectored vaccines include headache, feverishness, myalgia, arthralgia, fatigue and malaise. Generally volunteers report a transient flu like illness within 24 hours of vaccination with ChAd63 which resolves completely within 48hrs. It is anticipated that the majority of systemic adverse events post ChAd63 ME-TRAP will be mild in intensity. No vaccine related serious adverse events have been seen with ChAd63 ME-TRAP.

During the manufacturing process of ChAd63 CS, a biocide named Kathon is used. Kathon is added to body washes, conditioners, liquid soaps, shampoos and wipes as a preservative. The

maximum dose is 0.1% for 'rinse off' products and for 'leave on' products it is 0.05%. It has been approved by regulatory authorities throughout the world as a preservative in these products. As a skin sensitiser it is known to cause contact dermatitis. An internal study was set up to look at the levels of Kathon that were removed during the final purification step of buffer exchange. This study utilized high performance liquid chromatography and showed that trace amounts of Kathon may be left on the column after carrying out the rinse and sanitisation steps. However, the study confirmed greater than 99.9975% removal of Kathon to approximately 30 fold less than the limits for 'leave on' products containing Kathon. We will exclude anyone from the study with a history of clinically significant contact dermatitis or sensitivity to Kathon.

There are no additional safety concerns arising from clinical trial experience with the administration repeated doses of ChAd63 ME-TRAP. As described in the Investigator Brochure for ChAd63 ME-TRAP, five volunteers have received a second dose of ChAd63 ME-TRAP after vaccination with ChAd63 ME-TRAP followed by MVA ME-TRAP (VAC033 clinical trial, completed). In the ongoing VAC043 clinical trial, 12 volunteers have received two sequential doses of ChAd63 ME-TRAP and a further 6 have received three sequential doses.

### **MVA ME-TRAP**

More than 700 volunteers have received MVA ME-TRAP in the United Kingdom (UK), Senegal and the Gambia. Most volunteers developed erythema (or discolouration in African skin) and swelling post vaccination which in the majority of cases was mild to moderate in nature. This was accompanied by discomfort, warmth, itching and scaling which typically resolved to a faint flat papule. Intramuscular administration of MVA ME-TRAP has significantly less local reactogenicity than intradermal. Local AEs are likely to be mild in nature and should resolve rapidly, although there is the possibility of moderate arm pain in some cases. Common systemic adverse events post MVA vectored vaccines include headache, feverishness, myalgia, arthralgia, fatigue, and malaise. Generally volunteers report a transient flu like illness within 24 hours of vaccination with MVA which resolves completely. It is anticipated that the majority of systemic adverse events post MVA ME-TRAP will be mild or moderate in intensity. No vaccine related serious adverse events have been seen with MVA ME-TRAP.

### **Rabies vaccine**

Mild and self-limited local reactions such as pain at the site of injection, redness and swelling occur in 21–74% of vaccinees. Bleomycin and neomycin are used in the manufacturing process and therefore volunteers with a history of hypersensitivity to these drugs, or aminoglycoside antibiotics, will be excluded from the trial. Mild systemic reactions such as fever, headache, dizziness and gastrointestinal symptoms occur in 5–40%, and systemic hypersensitivity following booster injections in 6% of vaccinees, but are less common following primary immunization.

### **Duty to minimise risks to volunteers**

Adverse events are possible with any new vaccine. The risk is minimised by use of two candidate vectors chosen specifically for their good safety profile. Nevertheless, this study is designed to employ small numbers of closely supervised vaccinations. The comprehensive quality control, toxicology and manufacturing data and the absence of vaccine related serious adverse events with ChAd63-MVA ME-TRAP in phase I studies in Oxford, Kenya and the Gambia provide evidence of the minimal nature of risk in this study. However anaphylaxis is estimated to occur at a frequency at 1 in  $10^5$  to  $10^6$  with all vaccines. Should such a rare event occur, resuscitation facilities will be available to manage the reaction. As with any vaccine, Guillain-Barré syndrome or immune-mediated reactions that can lead to organ damage including serious allergic reactions may occur but this should be extremely rare has not been seen to date with ChAd63-MVA ME-TRAP.

